## Abstract

**Introduction:**

Hypoglycaemia is a harmful potential complication in people with type 1 diabetes mellitus (T1DM) and can be exacerbated in patients receiving treatment, such as insulin therapies, by the very interventions aiming to achieve optimal blood glucose levels. Symptoms can vary greatly, including, but not limited to, trembling, palpitations, sweating, dry mouth, confusion, seizures, coma, brain damage or even death if untreated. A pilot study with healthy (euglycaemic) participants previously demonstrated that hypoglycaemia can be detected non-invasively with artificial intelligence (AI) using physiological signals obtained from wearable sensors. This protocol provides a methodological description of an observational study for obtaining physiological data from people with T1DM. The aim of this work is to further improve the previously developed AI model and validate its performance for glycaemic event detection in people with T1DM. Such a model could be suitable for integrating into a continuous, non-invasive, glucose monitoring system, contributing towards improving surveillance and management of blood glucose for people with diabetes.

**Methods and analysis:**

This observational study aims to recruit 30 patients with T1DM from a diabetes outpatient clinic at the University Hospital Coventry and Warwickshire for a two-phase study. The first phase involves attending an inpatient protocol for up to 36 hours in a calorimetry room under controlled conditions, followed by a phase of free-living, for up to 3 days, in which participants will go about their normal daily activities unrestricted. Throughout the study, the participants will wear wearable sensors to measure and record physiological signals (eg, ECG and continuous glucose monitor). Data collected will be used to develop and validate an AI model using state-of-the-art deep learning methods.

**Ethics and dissemination:**

This study has received ethical approval from National Research Ethics Service (ref: 17/NW/0277). The findings will be disseminated via peer-reviewed journals and presented at scientific conferences.

**Trial registration number:**

NCT05461144.

STRENGTHS AND LIMITATIONS OF THIS STUDYThis two-phase study will obtain data in both the controlled environment of a metabolic chamber and in free-living conditions, overcoming limitations of previous studies limited to controlled conditions.The second phase of the protocol has been designed with non-compliance in mind in order to determine how a model developed in controlled settings works with real-world data.This is a single-centre observational study aiming to recruit from the local population without discrimination of characteristics such as sex, ethnicity or race, which may limit the generalisability of the results.

## Introduction

Type 1 diabetes mellitus (T1DM) is a chronic disorder caused by autoimmune damage to the insulin-producing pancreatic beta cells, leading to elevated blood glucose concentration (hyperglycaemia).^1^ T1DM requires exogenous insulin treatment,^2^ of which hypoglycaemia is a potential side effect.^3^ The prevalence of T1DM globally is 5.9 per 10 000 with the incidence of 15 per 100 000 people.^4 5^ In the UK, the prevalence is reported as fifth highest with 8.6%, and incidence of T1DM is rising 5% every year.^5^ There is no cure for diabetes; therefore, effective management can be pivotal in reducing risk of adverse events as well as delay the onset of long-term complications.^6 7^

The self-monitoring of blood glucose (SMBG) can play a key role in effective management of diabetes. SMBG can empower patients to adhere to lifestyle interventions, such as changes to diet and exercise regimen, as they have access to immediate feedback on the effects.^8^ Active participation from the patient in their care has been shown to improve outcomes such as reducing the risk of diabetic complications.^9^ Current methods for glucose monitoring have several limitations. The most common method for SMBG is an invasive ‘finger-prick test’ in which a small sample of blood is collected from the fingertip and analysed by a handheld device called a glucometer. This invasive procedure has several documented barriers preventing SMBG such as inconvenience, cost and discomfort.^10^ Moreover, the devices and associated consumables are prone to error if not operated correctly,^11^ requiring repeat attempts and generating unnecessary waste. Hypoglycaemia typically occurs during sleep,^12^ and those receiving insulin therapy are at increased risk due to a combination of factors such as impaired counter-regulatory hormone response and warning symptoms going unobserved.^13^ This presents an obvious limitation to the effectiveness of an invasive ‘finger-prick test’ as a tool for SMBG. An alternative to ‘finger-pricking’ are continuous glucose monitoring (CGM) devices, which require a small cannula inserted in the top layer of skin to continuously measure glucose in the fluid between the cells. They can be described as minimally invasive as after the initial fitting, they are routinely worn continuously for up to 14 days. However, despite being shown to be a beneficial tool for SMBG, national clinical guidelines for the UK do not recommend routine use of CGM devices for the management of T1DM due to insufficient evidence demonstrating their efficacy and cost-effectiveness.^14^

It has been demonstrated, by this group^15 16^ and others,^17–19^ that glycaemic events can affect certain cardiac characteristics, which can be extracted from readings of the electrical activity of the heart, the ECG. With increasing availability of wearable devices for tracking physiological signals, studies have been undertaken to investigate prediction of blood glucose concentration or glycaemic event detection using artificial intelligence (AI), by combining data or features extracted from the ECG with blood glucose measurements. Such an approach would address the need for non-invasive continuous blood glucose monitoring. Studies have shown promising predictive performance based on data collected from healthy subjects^15 16 20–22^ or adolescent patients with T1DM.^19 23^ In a review of techniques for detecting hypoglycaemia, Diouri *et al* note that the use of ECG-based techniques has only been investigated in small cohort trials, and that the success of such approaches relies on further, ideally larger, trials and validation in patients with diabetes and cardiac diseases.^24^

This protocol expands on an initial pilot, results of which are published,^15^ which made opportune use of applicable secondary data collected for a separate study^25^ on healthy elderly men. The aim of the pilot was to use the data to create a personalised AI model for the detection of nocturnal hypoglycaemia. The developed and validated deep learning model achieved 90% for specificity (ability to identify true positives) and sensitivity (ability to identify true negatives), which are clinically relevant metrics in relation to diagnosis of disease.^26^ The aim of this protocol is to build on this initial work, by obtaining new data to validate the technique for people with diabetes and test its applicability beyond controlled conditions, to that of normal living conditions.

### Study objectives

The purpose of this observational study is to acquire continuous physiological data from adults with T1DM over a period of several days. Data obtained from wearable sensors and recorded in diaries to track lifestyle activities will be used to carry out our primary and secondary objectives.

#### Primary objective

The primary objective of this study is to further develop and validate in a new population (T1DM) our previously developed AI approaches for non-invasive hypoglycaemia detection. We will extract and analyse ECG-derived features from the raw signal and determine their relationship with the glycaemic status. State-of-the-art algorithms will be used to create a mathematical mapping from the ECG-derived features to the glycaemic status.

#### Secondary objective

To examine the impact of physical activity and diet on glycaemic events and incorporate relevant features into the model.

## Methods and analysis

### Study setting

This two-phase observational study will be conducted at the Human Metabolism Research Unit (HMRU) and in free-living conditions. During phase 1, the participants attend an inpatient protocol at University Hospital Coventry and Warwickshire (UHCW) in a calorimetry room for up to 36 hours. The calorimetry room is a controlled environment, which allows for precise regulation of parameters such as ambient temperature, air pressure, humidity and subject behaviour enabling us to obtain high-quality baseline ECG and glucose data from the wearable sensors. In phase 2, the same sensors will be used to collect data under free-living conditions, for a period of up to 3 days, during which the participants are free to go about their normal daily activities without restriction. Participants will be asked to complete diaries for daily activity, food intake and sleep.

### Inclusion and exclusion criteria

The study will be open to all adult individuals living independently with T1DM who are comfortable with a stay in a calorimetry room. The inclusion and exclusion criteria are summarised in box 1.

Box 1Inclusion and exclusion criteria
**Inclusion criteria**
Aged 18 years or older.Without acute illness or ongoing clinical investigation.Participants with an ongoing medical condition will only be included after detailed consultation with clinical and dietetics members of the team.
**Exclusion criteria**
Children (under 18 years).Any adult who lacks decisional capacity.Claustrophobic and/or isolophobic patients, or those with needle phobia.Individuals who have undertaken recent abnormal exercise, radiation exposure within the preceding 24 hours of entering the whole-body calorimeter and feeling unwell in any way.Any medical/endocrine problem that could affect energy expenditure (eg, thyroid problems, Cushing’s syndrome).Chronic inflammatory disorders like rheumatoid arthritis, or long-term use of steroids or other immunomodulators like ciclosporin, azathioprine and beta blockers.Currently actively losing weight.Depression or any psychiatric illness.

### Enrolment procedure

Participants will be recruited from the Warwickshire Institute for the Study of Diabetes, Endocrinology, and Metabolism Clinic at UHCW. We aim to recruit up to 30 adult patients with T1DM who may enrol in either or both phases of the study. The process of identifying potential participants began in September 2022 and the first session took place in December 2022. Participant recruitment will be an ongoing process, expected to conclude in September 2023. All participants will receive a participant information sheet and written informed consent will be obtained.

### Sample size

As this is an observational study, an exact sample size calculation is not possible. A target of 30 participants will be enrolled, based on a pragmatic approach, which ensures sufficient data are available for analysis. Full participation in the protocol will yield 108 hours of continuous data per participant. We aim to capture the daily blood glucose fluctuations known as glycaemic variability,^27^ a feature of impaired glucose metabolism. However, it is not possible to anticipate how many hypoglycaemic episodes will be recorded. ECG data, labelled with corresponding glucose concentration, will be analysed in excerpts of variable length from individual heartbeats (cardiac cycles) to several minutes, resulting in a large sample size.

### Study protocol

#### Calorimetry room

The participant will stay in the calorimetry room for up to 36 hours, during which there will be set times for meals, light exercise and rest. Meals will be provided with known total energy and macronutrient content. Water will be provided ad libitum. While in the calorimetry room, wearable sensors will record physiological data continuously.

Other activities will be performed during this time, specifically: (a) up to 12 serial blood samples of 30 mL will be obtained from a peripheral venous catheter inserted at the beginning of phase 1 to measure venous glucose and insulin concentration, (b) finger-prick blood samples will be taken periodically for capillary glucose measurements, (c) up to 12 saliva samples will be taken to analyse salivary concentration of cortisol and melatonin, (d) all urine will be collected as voided for protein oxidation analysis, (e) movement and activity will be assessed by motion sensors, (f) simple questionnaires will be used to measure food intake and activity as well as subjective aspects such as appetite, satiety and wellness, and (g) daytime blood pressure will be monitored using an ambulatory blood pressure monitor (hourly readings).

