#### Covariates

The autonomic nervous system is responsible for maintaining homeostasis and regulates processes such as blood pressure,^36^ digestion,^37^ metabolism^38^ and circadian rhythm,^39^ all of which may affect cardiac function and show as changes in the ECG morphology.^40–43^ Additionally, exercise can affect the QT interval, that is the ECG section representing ventricular depolarisation, due to exercise-induced autonomic response.^44^ During phase 1 of the study, daytime blood pressure will be monitored, and the calorific value and macronutrient composition of meals will be recorded. Additionally, exercise sessions will be scheduled throughout the phase. Throughout the free-living phase, all meals, exercise duration and intensity, and sleep times will be recorded by the participant. The data collected via this protocol enable us to examine how the covariates relate to the outcome of interest, that is, the glycaemic status, by performing statistical tests such as analysis of variance.^45^ The recording of mealtimes, exercise and sleep enables the data to be analysed during distinct periods of interest such as post-exercise or postprandial.

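### The tests named for the secondary objective carry no time-of-day term, so day-night differences in glycaemia can be reported as exercise or diet effects

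*Protocol article*

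**What the plan says.** The Secondary objective section of the protocol article reads "To examine the impact of physical activity and diet on glycaemic events and incorporate relevant features into the model". The method is in the Covariates section, which says the data allow the investigators to "examine how the covariates relate to the outcome of interest, that is, the glycaemic status, by performing statistical tests such as analysis of variance". No model terms are listed.

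On when the exposures occur, the Calorimetry room section says "there will be set times for meals, light exercise and rest", and the Covariates section adds: "Additionally, exercise sessions will be scheduled throughout the phase". Neither gives clock times or says whether the times are the same for every participant. The Study setting section leaves activity unrestricted for up to 3 free-living days, with meals, exercise and sleep recorded by the participant.

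On when the outcome occurs, the Introduction states: "Hypoglycaemia typically occurs during sleep".

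The Covariates section does mention circadian rhythm, but as an influence on cardiac function and the ECG. It is not named as something that exercise, meals and glycaemic status share. The same section says that recording mealtimes, exercise and sleep allows distinct periods, such as those after exercise or meals, to be analysed.

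**The concern.** People exercise and eat when awake. If hypoglycaemia concentrates in sleep, as the article itself says, then time of day is linked to both exposure and outcome. A plain comparison of exposed hours with the remaining hours then contrasts day with a mixture of day and night. An exposure with no effect can appear to lower or raise the frequency of glycaemic events.

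The secondary objective speaks of impact, and covariates judged relevant go into the model. A misattributed day-night difference could therefore reach both the reported findings on activity and diet and the choice of features.

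A narrower difficulty belongs to phase 1. If the timetable is common to all participants, the hours after exercise are the same clock hours for everyone. There is then no unexposed observation at those hours to compare with.

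**Working it through.** **The plan's own figure.** Full participation gives 36 h + 3 × 24 h = 108 h, as the Sample size section states. Phase 2 supplies 72/108 = 67% of these hours, so the objective does not rest on phase 1 alone.

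**Check 1: odds ratio with no true effect.** Assumed, not in the documents: 4 post-exercise hours per day, all in daytime; an 8 h night; constant risk within day and within night. The other 20 hours are 8 night and 12 day.

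- Risk in other hours = (8 × night + 12 × day)/20
- Odds ratio = odds(day)/odds(other hours)

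| Night risk | Day risk | Other hours | Odds ratio |
|---|---|---|---|
| 8% | 2.5% | (64 + 30)/20 = 4.7% | 0.0256/0.0493 = 0.52 |
| 6% | 2% | (48 + 24)/20 = 3.6% | 0.0204/0.0373 = 0.55 |
| 4% | 2% | (32 + 24)/20 = 2.8% | 0.0204/0.0288 = 0.71 |
| 5% | 3.5% | (40 + 42)/20 = 4.1% | 0.0363/0.0428 = 0.85 |
| 3% | 3% | (24 + 36)/20 = 3.0% | 1.00 |
| 2% | 4% | (16 + 48)/20 = 3.2% | 0.0417/0.0331 = 1.26 |

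The last two rows show that the direction follows from the assumed risks. If the comparison is limited to waking hours, both sides have the day risk and the ratio is 1.00 in every row.

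**Check 2: simulation with a true exercise effect of zero.** From the documents: 30 participants, 15-minute glucose values, 36 h and 72 h phases. Assumed: a 24-hour cosine in glucose peaking mid-afternoon; within-person SD 2 mmol/L with autocorrelation 0.95 between readings; 2 h post-exercise windows from 10:30 and 16:30 for everyone in phase 1; one exercise bout a day at a random time between 07:00 and 21:00 in phase 2. The analysis used participant fixed effects and cluster-robust standard errors, with 40 runs per setting.

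Mean spurious exercise effect in mmol/L (share of runs with p < 0.05):

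| Amplitude (mmol/L) | 0 | 0.5 | 1 | 2 |
|---|---|---|---|---|
| Phase 1, no time term | -0.01 (5%) | 0.31 (65%) | 0.63 (100%) | 1.22 (100%) |
| Phase 2, no time term | -0.05 (3%) | 0.28 (35%) | 0.62 (93%) | 1.21 (100%) |
| Both, no time term | -0.03 (0%) | 0.32 (90%) | 0.64 (100%) | 1.26 (100%) |
| Phase 1, 07:00–23:00 only, no time term | -0.01 (3%) | 0.15 (33%) | 0.25 (70%) | 0.54 (100%) |

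- With a smooth 24-hour term, the effect lies between -0.03 and +0.02 at every amplitude, in each phase and combined.
- With quarter-hour clock terms, it lies between -0.03 and +0.03 in phase 2 and in the combined data.
- In phase 1 alone under the common timetable, the quarter-hour model cannot be fitted: clock time predicts exercise completely (R² = 1.00).

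The smooth term performs well here partly because the simulated rhythm is itself a cosine. In phase 1 alone, its success depends on that assumption about shape. With 40 runs per setting, the rejection shares are approximate.

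**The case against.** The strongest reply is that the article fixes very little. Analysis of variance is only an example, no terms are listed, and a condensed article may leave adjustment terms to a fuller document. No section says that post-exercise hours will be compared with a pool containing the nights. Sleep is recorded, with a standardised diary in free living, so nights can be set apart. Lifestyle covariates are also meant as predictors, and a variable that tracks time of day may predict legitimately; the Data modelling section tests the model subject-wise on unseen data.

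Much of this stands. A missing term alone would not be a point worth raising. Two things remain. The objective asks for impact, which predictive validation does not establish. And where the article does discuss circadian rhythm, it treats it as acting on the ECG only, while its own Introduction ties the outcome to sleep. Recording sleep makes the right comparison possible but does not commit the analysis to it.

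A reader might also infer that the set times in phase 1 are the cause. The simulation does not support that: unscheduled daytime exercise in phase 2 produces nearly the same spurious effect. What is peculiar to phase 1 is that exposure and clock time cannot be separated, and that requires a common timetable. The article does not state one; the Patient and public involvement section says only that phase 1 is a standard protocol of the unit.

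**Conclusion.** The point holds as a risk in the named analysis, in both phases. A test of exercise or diet against glycaemic status without a time-of-day term can report day-night differences as effects of the exposure. At the assumed risks with night above day, a null exposure shows odds ratios from 0.52 to 0.85; with equal risks there is no bias, and with day risk higher the ratio exceeds 1. In the simulation, the spurious difference is about 0.3 to 1.2 mmol/L for assumed amplitudes of 0.5 to 2 mmol/L.

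It would go too far to say that the study will report exercise or meals as protective. That reading needs a pooled comparison, night and day risks and a timetable that the documents do not give. It also treats silence about model terms as a decision to omit them.

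The limit on phase 1-only contrasts is conditional on a common timetable. The change is worth making: it is cheap, and it settles what the secondary objective can claim.

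**What to change.** In the Covariates section, replace the plain analysis of variance for the secondary objective with a model of glycaemic status that has:

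- participant terms, since participants may join either or both phases and contribute unequal hours;
- a smooth 24-hour term or clock-hour terms.

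Compare post-exercise and postprandial windows with waking hours only, and use the recorded sleep times to analyse nights separately. The waking-hours restriction should accompany the time term and not replace it: on its own it left 0.15 to 0.54 mmol/L in the phase 1 simulation.

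State whether the phase 1 timetable is the same for all participants. If it is, present exercise and diet contrasts from phase 1 alone as descriptive and draw inference from phase 2 or the combined data.

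Matching to the same clock hours on exposure-free days can be offered as a sensitivity analysis but should not be required. Free living lasts at most 3 days and meals occur daily, so matched hours would be scarce. Comparing nights after exercise with other nights is thin for the same reason.

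The cost is wording and modest analyst time. No new data are needed. Fewer hours contribute and intervals for the secondary objective become somewhat wider.

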#### Free-living

While free-living, the participant will continue to wear the monitoring devices to record ECG and glucose concentration. If tolerated, participants will also be fitted with an ambulatory blood pressure monitor for the first 24 hours of the free-living phase. Instructions will be provided on how to affix and operate the devices. During this time, participants will also be required to keep brief diaries detailing physical activity, food intake and sleep. The first is a daily activity diary, to be completed at the end of each day, detailing: any device removal and replacement, physical activity, food intake, alcohol intake and caffeine intake. The second is a standardised sleep diary, the Consensus Sleep Diary-M,^28^ to be completed on waking in the morning.

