#### ECG

Medtronic Zephyr BioPatch is a CE-marked device, indicating that the product complies with European Union safety, health and environmental requirements, which operates across one lead within an ECG amplitude range between 0.25 and 15 mV, with a sampling frequency of 250 Hz. The device will be affixed to the wearer’s skin via two electrodes placed in the centre of the chest. It can also be worn in a secondary configuration attached to a fabric harness, which is worn across the chest if the electrodes are not tolerated. The Zephyr BioPatch also has additional sensors to record physiological parameters such as activity levels, posture and breathing rate, which are all reported at 1 Hz.^30^ The device will be removed before bathing, showering or swimming, and reaffixed afterwards. The battery is rated for 35 hours of continual use. Each participant will be provided with fully charged devices for the free-living phase of the study.

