#### Data modelling

The inherent part of the project is to develop AI models for detecting glycaemic events and inferring them with physical activity and diet. The state-of-the-art AI models vary from traditional machine learning models (such as Support Vector Machines, Decision Trees, etc) to advanced deep learning-based models.^46^ Traditional machine learning models have the capability to train static features for the development of explanatory models, whereas deep learning models can train raw ECG signals based on spatial and temporal context. The deep learning models will be built upon earlier work developed for healthy subjects.^15^ We aim to develop and validate hypoglycaemia detection models that incorporate lifestyle trends such as activity levels and sleep patterns using metrics provided by the sensors and reported in the diaries. For a model to be clinically useful, it should demonstrate generalisability. Therefore, we will test the model on unseen data using a subject-wise cross-validation approach.^47^

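### Free-living mealtimes, and exercise done with the ECG device off, come from an end-of-day diary but are used to define postprandial and post-exercise periods

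*Protocol article*

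**What the plan says.** The Free-living section describes two diaries. The sleep diary is filled in on waking and is not at issue. The daily activity diary is "to be completed at the end of each day, detailing: any device removal and replacement, physical activity, food intake", and it also covers alcohol and caffeine.

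The Covariates section names the participant as the source: "Throughout the free-living phase, all meals, exercise duration and intensity, and sleep times will be recorded by the participant". It then gives the use: "The recording of mealtimes, exercise and sleep enables the data to be analysed during distinct periods of interest such as post-exercise or postprandial". These data serve the secondary objective, "To examine the impact of physical activity and diet on glycaemic events and incorporate relevant features into the model".

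Two other statements bear on the point. According to the ECG section, the BioPatch has "additional sensors to record physiological parameters such as activity levels, posture and breathing rate, which are all reported at 1 Hz". The Study setting section confirms that it is worn in free-living: "In phase 2, the same sensors will be used to collect data under free-living conditions, for a period of up to 3 days". In the calorimetry room, by contrast, "there will be set times for meals, light exercise and rest".

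**The concern.** A postprandial period is a stretch of time counted from the start of a meal, so it is only as accurate as the recorded mealtime. The article asks for that time in an entry made once a day, after the events. The signals to be cut into periods are much finer: the data analysis sections speak of excerpts of 1, 2 or 5 minutes and of 15-minute groups matched to the glucose sensor.

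If recorded mealtimes are off by tens of minutes, some postprandial time is labelled as something else and an equal amount of other time is labelled postprandial. Where the error is unrelated to glucose, this pulls the estimated association of diet with glycaemic events towards zero. It also degrades mealtime as a model feature. Exercise carried out with the device off has the same problem. A clock time that was not noted when the event happened cannot be recovered at analysis.

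**Working it through.** **1. How much of the data is affected.** The Sample size section gives 108 hours for full participation. Phase 1 lasts up to 36 hours and phase 2 up to 3 days: 36 + 3 × 24 = 36 + 72 = 108 hours, which reproduces the stated figure. Free-living is 72/108 = 66.7% of this. Participants may enrol in either phase, so for someone who joins only phase 2 all of the data are free-living.

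**2. Which event times have a source other than the diary in free-living.**

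| Event | Record described | Depends on the end-of-day entry? |
|---|---|---|
| Meals, snacks | Activity diary | Yes; no device described records eating |
| Exercise, device worn | Diary and 1 Hz activity signal | No; can be timed from the signal |
| Exercise, device off (e.g. swimming) | Diary | Yes |

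Reading mealtimes off the glucose trace would be circular, because glycaemic status is the outcome.

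**3. What a timing error does to a window.** The article gives neither a postprandial window length nor an error size, so everything in this step is assumed. Let the true window have length W and let the recorded start be wrong by e minutes. The share of true postprandial time that falls outside the recorded window is min(|e|, W)/W. With e normal, mean 0 and standard deviation SD, the expected share is E[min(|e|, W)]/W. Without the cap, E|e| = SD × √(2/π) = 0.798 × SD.

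For W = 120 minutes:

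- SD 15: 12.0/120 = 10%
- SD 30: 23.9/120 = 20%
- SD 60: 46.9/120 = 39% (uncapped 47.9; the cap removes about 1 minute)

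A simulation of one million draws gave 0.100, 0.199 and 0.389. The same simulation for other window lengths:

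| Assumed window | SD 15 min | SD 30 min | SD 60 min |
|---|---|---|---|
| 60 min | 19.9% | 38.9% | 63.0% |
| 120 min | 10.0% | 19.9% | 38.9% |
| 180 min | 6.6% | 13.3% | 26.5% |

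**4. Against the plan's own resolution.** An error of 30 minutes spans 30/15 = 2 glucose-sensor intervals, or 30/5 = 6 five-minute excerpts.

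**The case against.** The best defence is that the article fixes when the diary is completed and does not say that times are entered from memory. Notes during the day are not forbidden, the Covariates section does speak of mealtimes being recorded, and the detailed diary instructions may sit in the full protocol, which is not shown. This stands in part: entry from memory is the natural reading of an end-of-day diary, not a stated fact. But the completion time is an explicit choice in the article, so the point is not about an omitted detail.

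A second defence is that postprandial and post-exercise periods are offered as examples, with no window fixed, and that same-day reports may be accurate to within minutes. That limits the size of the problem, and nothing in the article says which SD applies. A third is burden: participants already scan the glucose sensor and swap and reattach the ECG device. That is fair, but the extra task is small.

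A reader might infer more than the text supports:

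- **That all exercise timing rests on recall.** It does not. The activity signal runs at 1 Hz while the device is worn, and the Data modelling section plans on "using metrics provided by the sensors and reported in the diaries".
- **That late recording of device removals harms these analyses.** Removals do not define the periods, and they should mostly show as gaps in the signal, although the article does not say that gaps will be found this way.
- **That a difference in diet effects between phases would be an artefact.** No such comparison is planned. The interest in real-world data concerns how the analysis and model perform there.
- **That diary entries are shaped by glucose values seen earlier in the day.** This is speculation. Participants can also see glucose before a meal, so noting times at the event would not remove it.

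**Conclusion.** The point holds in a narrow form. In free-living, up to 72 of 108 hours per participant, mealtimes and the times of device-off exercise come from a diary completed at the end of the day, while the analysis uses such times to place postprandial and post-exercise windows. The likely effect is weaker diet and activity associations in the secondary objective. The primary objective, detection of hypoglycaemia from the ECG, is touched only where mealtime enters the model as a feature.

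The size is unknown. The range of 10% to 39% rests wholly on an assumed 2-hour window, normal error and SDs of 15 to 60 minutes; it shows how sensitive the windows are and does not estimate what will happen here. The article contains no error or contradiction on this point. It prescribes a procedure for which a better one is available at little cost.

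**What to change.** Amend the Free-living section so that participants note the clock time of each meal or snack, and the start and stop of any exercise done with the ECG device off, when it happens. Keep the end-of-day entry as a check that nothing was missed. State in the Covariates section that other exercise bouts, and periods when the device is not worn, are timed from the BioPatch signal, with the diary used to explain them.

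The cost is a change in the diary instructions and slightly more effort for participants. No new device or visit is needed. Data already collected under the present instruction cannot be corrected, so it helps to record which diary instruction each participant followed.
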